##### Postoperative analgesia

Electronic parent-controlled intravenous analgesia (PCIA) pumps (CPE-101, Fornia Medical Equipment Co., Ltd., Zhuhai, China) will be used for all participants in the two groups in 2 days after surgery. The PCIA regimen is sufentanil 0.04 μg/kg/ml and 0.1 mg/kg tropisetron in normal saline 200 ml. A bolus of 1 ml on demand with a lockout interval of 15 min was set, with no background infusion. The guardians of patients will be trained in advance to use the electronic pump. Acetaminophen 15 mg/kg orally will be given to patients in both groups four times daily (maximum dose of 2 g per 24 h). If the patient’s NRS pain score is >6 or if rescue analgesia is needed, dezocine (0.1 mg/kg, maximum dose of 5 mg) will be given.

### Endpoints

#### Primary endpoint

The primary outcome was a joint endpoint of area under the curve (AUC) of numerical rating scale (NRS) score over time and opioid consumption in postoperative 24 h. NRS score (0 = no pain and 10 = the worst pain) at rest was measured at 0.5 h, 3 h, 6 h, 9 h, 12 h, and 24 h after surgery. The AUC was used to add temporality to the pain measure. Sufentanil consumption was measured as the number of PCIA boluses administered from 0 to 24 h postoperatively in boluses, which will be extracted from the electronic PCIA pump records.

### Data collection

Patient demographics (age, sex, body mass index), ASA status, comorbidities, number of fused levels, and Cobb’s angle will be collected. The following intraoperative data will be collected: duration of surgery (form incision to closure), duration of anesthesia (from induction to extubation), intraoperative medications, blood loss and transfusion, and fluid balance. Outcome variable will be recorded according to the follow-up plan. Case report forms will be used to collect data and will be kept timely, correctly, and securely, and monitored by the ethics committee of our institution, and the data monitoring committee every year, which is set up by Beijing Children’s Hospital with members have no interest relationship with the study. The process will be independent from investigators. Only authorized researchers will have access to the final trial dataset.

### Statistical analysis

#### Sample size calculation

To determine the sample size for the primary outcome, we treated the NRS score as a continuous variable. Our pilot investigation showed the AUC of 24 h-NRS score of 82 ± 21 at 24 h after surgery for the control group and 63 ± 25 for the ESPB group. With a 5% significance level and a power of 90%, we calculated that each group should contain at least 33 patients. In the pilot study, the number of cumulative 24-h PCIA boluses was 25 ± 6 for patients in the control group and 18 ± 9 in the ESPB group. With a significance level of 0.05 and a power of 90%, 27 patients were estimated per group. The larger sample size of 33 patients in each group was chosen, which we increased to 37 to allow for 10% dropouts. The sample size was estimated by PASS software (version 15.0; NCSS PASS, UT, USA).

#### Endpoint analysis

The primary joint outcome was the AUC of NRS score at rest over time and opioid consumption measured by the number of PCIA boluses in postoperative 24 h. We defined the between-group difference of the primary analysis to be significant only when the difference of NRS and PCIA boluses are both associated with *p* < 0.05. Otherwise, the presence of *p* > 0.05 on any outcome indicated unsignificant pain relief of ESPB compared to the control group. An independent two-sample *t* test or Mann‒Whitney *U* test will be used based on the distribution of variables. The NRS scores and PCIA boluses up to 48 h after surgery and the intraoperative hemodynamics at different time points will be analyzed using repeated-measures two-factor analysis of variance (ANOVA) with a Bonferroni correction or one-way ANOVA as well as a generalized estimated equation (GEE) model as appropriate. For baseline characteristics and other continuous outcomes measured at one time point, two-sample *t* tests or Mann‒Whitney *U* tests will be performed. Episodes of complications will be analyzed by the chi-square test or Fisher’s exact test. The primary analyses will be conducted by intention-to-treat, and sensitivity analysis will be performed on a per-protocol basis.

##### Descriptive and analytical statistics

Continuous data are presented as the mean (± standard deviation (SD)) or median (interquartile range (IQR)) and analyzed by two-sample *t* test or Mann‒Whitney *U* test based on the distribution of variables, as determined by the Shapiro–Wilk test. Categorical data will be reported as numbers (percentages) and compared by the chi-square test or Fisher’s exact test. A two-tailed *P* value less than 0.05 will be regarded as statistically significant. The statistical analyses will be performed with the SPSS 25.0 statistical package (IBM SPSS Inc., Chicago, IL, USA).

#### Missing values

Patients with missing data on the primary outcomes will be excluded from analysis. For the baseline variables or secondary outcomes, missing data will not be replaced. Data from patients with missing values on primary outcomes will be analyzed in sensitive analysis, and missing values will be imputed with the median for each respective time point.

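### The primary analysis is labelled intention-to-treat but drops patients with missing primary data, and the only missing-data check is an under-specified single median imputation

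*Protocol article*

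**What the plan says.** Endpoint analysis sets the population: "The primary analyses will be conducted by intention-to-treat, and sensitivity analysis will be performed on a per-protocol basis". Missing values then sets the handling of incomplete data: "Patients with missing data on the primary outcomes will be excluded from analysis". Those patients return only in a sensitivity analysis, in which "missing values will be imputed with the median for each respective time point".

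Primary endpoint defines the pain component as the AUC of the NRS score, which "at rest was measured at 0.5 h, 3 h, 6 h, 9 h, 12 h, and 24 h after surgery". The opioid component is the 24 h count of PCIA boluses, taken from the electronic pump records. Endpoint analysis calls the result "significant only when the difference of NRS and PCIA boluses are both associated with" p < 0.05. The primary test is a two-sample t test or a Mann–Whitney U test, chosen by distribution. The GEE and repeated-measures ANOVA in the same section are for the time courses to 48 h and the haemodynamics, not for the primary comparison.

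Sample size calculation allows for 10% dropouts. The protocol gives no expected rate of missed NRS readings, no rule for an AUC with some readings missing, and no statement of whether the imputing median is pooled or by arm.

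**The concern.** An intention-to-treat analysis keeps all randomised patients in their allocated arm. Excluding patients because of something that happened after randomisation, here a missing outcome, does not. Both rules are fixed in the current text and they pull apart.

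The endpoint sharpens the problem. The AUC needs a series of six readings, and neither planned primary test can use a partial series. A child with five scores and a full pump record could therefore leave the primary analysis. Scores may be missed because a child is sedated, unwell or in severe pain, and those states can depend on the block. Success requires both components to be significant, so a distorted AUC comparison can decide the trial.

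The check offered for this risk ignores the patient's own other readings and carries no imputation uncertainty. The per-protocol analysis does not address missing outcomes.

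**Working it through.** **1. The plan's own figures.** Inputs from Sample size calculation: AUC 82 ± 21 (control) and 63 ± 25 (ESPB), difference 19; boluses 25 ± 6 and 18 ± 9, difference 7; alpha 0.05, two-sided; power 0.90. Power comes from the noncentral t distribution with noncentrality d / √((s₁² + s₂²)/n) and 2n − 2 degrees of freedom.

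- AUC, n = 33: 19 / √((441 + 625)/33) = 19 / 5.68 = 3.34, power 0.909.
- Boluses, n = 27: 7 / √((36 + 81)/27) = 7 / 2.08 = 3.36, power about 0.91.
- Dropout: 33 / 0.9 = 36.7, so 37 per group.

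The stated 33, 27 and 37 all reproduce. With all 37 per arm analysed, AUC power would be 0.937.

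**2. Patients excluded if any missed reading removes the patient.** The missing rate p per reading is an assumption, as is independence between readings. The excluded share is 1 − (1 − p)⁶.

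| p per reading | Excluded | Left of 37 per arm | AUC power |
|---|---|---|---|
| 2% | 11.4% | 32.8 | 0.90–0.91 |
| 3% | 16.7% | 30.8 | 0.89 |
| 5% | 26.5% | 27.2 | 0.85 |

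At 2% the 10% allowance is about used up; at 3% and above it is exceeded.

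**3. Effect of the median rule.** Simulation settings, all assumed: pilot means and SDs, normal readings, within-patient correlation 0.5, 37 per arm, imputation reading by reading as written, trapezoidal AUC from 0.5 to 24 h. The trapezoid weights are 1.25, 2.75, 3, 3, 7.5 and 6 (sum 23.5), so the 12 h and 24 h readings carry 13.5 / 23.5 = 57% of the AUC. The true difference is 19 and the nominal type I error is 5%.

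| Missing pattern | Pooled median: difference | By-arm median: type I error |
|---|---|---|
| Scattered misses, 2–5% per reading | about 18.6 to 18.2 | about 6% |
| 12 h and 24 h both missing at random in 20% of patients | 16.7 | about 8% |
| All six readings missing in 4 of 37 per arm | about 17 | about 8% |

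Separate runs of the scattered case put the by-arm error between about 5.4% and 7%.

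**4. Effect on the complete-case estimate.** When missingness is unrelated to pain, the complete-case difference stays at about 19 and only power falls. As an illustration of the other case, suppose the 12 h and 24 h readings are lost only in the control arm, mainly among children in more pain (20% of that arm, 10% overall). The complete-case difference is then about 15, the pooled-median result 15.8 and the by-arm result 16.8. The main analysis and its check err in the same direction, so agreement between them would reassure wrongly.

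**The case against.** **The label may be loose rather than wrong.** Some authors use intention-to-treat to mean analysed as allocated among those with data. That would reconcile the two sections, but the protocol does not say so, and the analysis would still be complete-case.

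**One missed reading need not remove the patient.** A trapezoidal AUC can be computed across a gap, and the Discussion already acknowledges interpolation between assessments. This stands: no sentence says that a single missed score makes the AUC missing. The exclusion rates above apply only on the plain reading of a rule with no provision for partial data. Independence also gives the larger count; clustered misses exclude fewer patients at the same rate.

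**Exposure may be small.** The primary window is 24 h in hospital, boluses come from the pump, and children unable to cooperate with pain assessment are not enrolled. This also stands, and it protects the bolus component in particular. The 10% allowance covers modest loss of numbers, though not selective loss.

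**Readings to resist.** A reader might infer that the main result is biased, or that the check will lose about 2 of the 19 points or inflate type I error to 8%. The documents support neither. Bias depends on a missingness mechanism and amount that they do not give. In step 3 the larger figures need heavy loss: all six readings in 4 of 37 per arm, or both late readings in a fifth of patients. Under random missingness the by-arm point estimate stays at about 19; its fault is understated variance.

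**Conclusion.** The conflict between the intention-to-treat label and the exclusion rule is in the text and needs no assumption. So are two gaps: what happens to a partly observed AUC, and which median is imputed.

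The numerical consequences are conditional. On the plain reading, with independent misses of 2% to 5% per reading, 11% to 26% of patients would leave the primary analysis and AUC power would be about 0.90 to 0.85. Bias in the estimate arises only if missingness is related to pain or sedation and differs by arm. With scattered misses the distortion in the median check is modest.

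Severity: should-fix. The rule governs who enters the primary analysis of a trial that must succeed on two endpoints, and it should be settled before unblinding so that neither the exclusions nor the type of median is chosen after the results are seen.

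**What to change.** - Analyse all randomised patients in their allocated arm, keeping every observed NRS reading and the pump-recorded boluses.
- Handle missing NRS readings by multiple imputation within arm, using the patient's other readings, boluses and rescue use, and compute the AUC afterwards. A likelihood-based repeated-measures model from which the AUC contrast is derived would serve equally well.
- State the rule for an AUC with some readings missing.
- Report the complete-case analysis as a sensitivity analysis.
- Replace the median-imputation check with a delta-adjusted one, in which imputed scores are shifted by stated amounts. The imputation or model above relies on missingness being explained by observed data, and the shift tests that.

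Cost: plan wording and a little more analysis work, possibly an SPSS add-on or another package. The sample size need not change, since 37 per arm meets the stated power if no more than about 10% of the information is lost. Trial conduct is unaffected.

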### Safety considerations

The researchers will adhere to the operation protocol strictly to minimize the risk of adverse events (AEs) and severe adverse events (SAEs). Medications are prepared and double-checked by specialized nurses. The operation of ESPB will be conducted by a fixed and experienced team under the extensive monitoring of vital signs to avoid AEs such as local anesthetic systemic toxicity. Experts are ready to provide immediate support if needed. For participants who are harmed during the investigation, the cost of treatment will be borne, and financial compensation will be paid in accordance with the relevant national regulations and laws.

### Oversight and monitoring

The ethics committee and data monitoring committee are appointed to oversight and monitor the project and provide advice on all aspects of the study. The PI will oversee the operational issues of the project. The whole research team will meet every month to check the progress of the trial. The data of AEs will be collected and recorded. Severe adverse events (SAEs) will be reported to the ethics committee and data monitoring committee, who will meet every 2 months to ensure the safety of the trial.

All relevant parties, including the investigators, IRB, trial registries, site staff, and other relevant authorities, will be notified of any modifications to the protocol during the entire trial period. The participants will be informed of relevant changes to the protocol as soon as possible or immediately in the event of major safety or efficacy concerns.

## Discussion

Typically, as the standard procedure for surgical management of AIS, PSF involves three to eight levels of spinal exposure, massive blood loss, and extensive muscle dissection, which causes severe postoperative pain,^28^ thus requiring high opiate usage [29,30]. In addition, because of the effect of sevoflurane on intraoperative neurophysiological monitoring (IONM) of movement, the large use of intraoperative opioids, usually remifentanil, seems to be necessary but may be associated with hyperalgesia in the postoperative period, further leading to a postoperative increase in opioids [31], and an increased risk of complications [32]. Physicians have taken an effort to decrease opioid prescriptions by using multimodal analgesia approaches, including neuraxial or regional techniques, in the postoperative period [33]. ESPB has earned its efficacy and reliability in adult patients undergoing lumbar spine surgeries [34], cervical spine surgeries [35], and lumbosacral spine [11,36] and thoracic spine surgeries [10]. Recent studies have even reported that ESPB shows more reliable spread and cover to the dorsal rami than to the ventral rami [37]. If it can be used for scoliosis surgery, there will be several advantages: it has no effect on IONM, provides stable hemodynamics, reduces blood loss, and, most importantly, reduces the pain and the use of opioids.

ESPB are feasible following our protocol. A single injection can block spinal nerves at multiple levels because of the extensive spread of LA in the musculofascial plane [9]. The dermatomal distribution of sensory loss by a single injection can cover the area from the parasternal to the midline of the lower back [38]. Because the number of segments invaded by idiopathic scoliosis is often greater and the lower thoracic segment ESPB may only spread to the L2–L3 level [37], we adhere to the following rule when choosing the plane of injection of ESPB: the midpoint of the involved segments (planned incision) is chosen in cases involving ≤ 5 segments. For example, for children undergoing fusion of L1−5 segments, we choose to make the injection at the L3 level, where the ESPB using 0.3% ropivacaine 0.5 ml/kg can subsequently diffuse to the L1−L5 levels to meet the surgical needs [39]. If fusion is planned for ≥ 6 segments, the incision is divided into two segments, and the midpoint of each segment is chosen as the injection site [24]. However, there are no pharmacokinetic data or solid conclusions on the maximal safe concentration and volume for ESPB so far [40]. The literature regarding pediatric use is even more limited. The volumes used in both our institution and previous publications are 0.3–0.5 mL/kg per side, with LA concentrations of 0.2% to 0.25% for infants and children, and 0.5% for adolescents [25]. However, it is imperative to emphasize that, to date, no pharmacokinetic data for ESPBs are available. This further reinforces the need to evaluate the safe maximal doses of concentration and volume for the age range [41].

In addition, the postoperative analgesia effect was illustrated by analyzing both the NRS score and PCIA boluses of opioids jointly in our study, since neither of the two ubiquitous outcomes of efficacy in trials of analgesics measured pain adequately when assessed alone [42]. The AUC-NRS adds a temporal dimension to the pain measurement, outbalances uneven measurement intervals, provides an integration of pain intensity versus time, and characterizes the trajectory of postoperative pain and analgesic drug efficacy more comprehensively. Compared with analyzing the discrete NRS score separately, this method increases statistical strength due to decreasing the risk of type 1 error in multiple significance tests. Additionally, the AUC-NRS is commensurable with opioid consumption, as it can fit along identical time intervals to better reflect the burden of pain over time [43].

However, no consensus has been reached regarding universal methods and the most appropriate statistical methods pertaining to outcome estimates in acute pain research. When applying the AUC-NRS method, potential erroneous interpolated estimates of pain during assessment intervals may occur. Additionally, clinically important indices such as the time to recurrence of pain, maximal pain experienced, and number of breakthrough pain episodes are not addressed.

In conclusion, pain management is a crucial aspect in the recovery of pediatric patients undergoing open spine surgery. To our knowledge, this study is the first to evaluate ESPB regarding efficacy in pediatric AIS patients undergoing PSF. The expected results of our study might prove the potential of ESPB to be recommended for perioperative analgesia in major open spine surgery.

## Trial status

The study is at the patient enrollment and data collection stage currently. The version of this study protocol is version 1.1 and was approved on 16 July 2023. Patient recruitment started on 1 September 2023 and is expected to be finished by 31 July 2024.

## Data Availability

The data including the full protocol, participant-level dataset, and statistical code will be available from the corresponding author upon request.

## Abbreviations

AIS: Adolescent idiopathic scoliosis
ASA: American Society of Anesthesiologists
AUC: Area under the curve
ESPB: Erector spinae plane block
IONM: Intraoperative neurophysiological monitoring
LA: Local anesthetic
NRS: Numerical rating scale
PACU: Post anesthesia care unit
PCIA: Parent-controlled intravenous analgesia
POD: Postoperative days
PONV: Postoperative nausea and vomiting
PSF: Posterior spinal fusion
QoR-15: Quality of Recovery-15 score
